### Trial schedule and follow-up

The follow-up plan includes both perioperative and long-term clinical outcomes (see Table 3). The clinical data to be collected will include preoperative baseline information, including demographic information, imaging studies (electrocardiogram, echocardiography), laboratory tests (including total platelet count, cardiac troponin I, and N-terminal pro-brain natriuretic peptide (NT-proBNP)), medication history, as well as primary and secondary endpoint data. Follow-ups for all participants are scheduled at 12 months, during which both primary and secondary outcomes, as well as safety, will be assessed.

**Table 3 Tab3:**
[figure not shown]
Schedule of recruitment, interventions, and assessments

*OCT* optical coherence tomography, *IVUS* Intravascular Ultrasound, *ECG* electrocardiography, *RA* Rotational Atherectomy

### Sample size

According to the literature, the probability of complications occurring during RA is 4%, 14% in the HSRA + LSRA group [18], and 24% at higher rotational speeds. A sample size of 175 achieves 80% power to detect an effect size (*W*) of 0.2353 using a 2-degree-of-freedom chi-square test with a significance level of *α* = 0.05 [29]. Considering a 15% dropout rate, the total required sample size is 210, with 70 participants per group.

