### Statistical analysis

All data will be statistically analyzed using SPSS version 22.0. Quantitative data will be presented as mean ± standard deviation (± s), with intergroup comparisons made using independent sample *t*-tests. Categorical data will be presented as number (percentage) [*n* (%)], with intergroup comparisons using the χ^2^ test. Logistic regression analysis will be applied to ascertain the correlation between coronary rotational speed and perioperative complications, as well as 1-year MACCE. Considering potential data missing and loss to follow-up, we will mainly use intention-to-treat (ITT) analysis and apply per-protocol (PP) dataset for sensitivity analysis. Besides, we will preset some subgroup analyses (e.g., based on patient age groups or lesion complexity) to verify results’ stability and explore special effect participants. To account for multiple comparisons, family-wise error rate (FWER) control methods will be applied where appropriate. Specifically, Bonferroni correction (adjusting the significance threshold to *α*′ = 0.025) and the Holm-Bonferroni procedure (a stepwise approach that improves statistical power while maintaining FWER control) will be used for primary analyses. To minimize unnecessary tests, only key comparisons (HSRA vs. LSRA; HSRA + LSRA vs. LSRA) will be included. When the sample size is limited, Holm’s method will be preferred over Bonferroni to optimize the balance between statistical power and error control. A *P* value of < 0.05 will be considered statistically significant. All statistical tests will be two-sided.

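### The stated 80% power belongs to a three-group chi-square at 0.05; of the two pairwise tests named for the primary analyses, HSRA + LSRA vs LSRA has only about 47–56% power under Holm (34–44% under Bonferroni).

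*Protocol article*

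**What the plan says.** **Sample size section.** Three complication rates are given: "the probability of complications occurring during RA is 4%, 14% in the HSRA + LSRA group", and "24% at higher rotational speeds". The 14% is tied to the hybrid arm and the 24% to higher speeds; the 4% is not tied to a named arm. The section continues: "A sample size of 175 achieves 80% power to detect an effect size". The effect size W and the test behind that figure are specified next: "0.2353 using a 2-degree-of-freedom chi-square test with a significance level of" 0.05. On enrolment the section adds: "Considering a 15% dropout rate, the total required sample size is 210, with 70 participants per group".

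**Statistical analysis section.** Categorical data are compared between groups with a chi-square test. Family-wise error control is applied where appropriate, and for the primary analyses two methods are named: "Bonferroni correction (adjusting the significance threshold to" 0.025, and Holm-Bonferroni. On which contrasts are tested, the section says that "only key comparisons (HSRA vs. LSRA; HSRA + LSRA vs. LSRA) will be included". Holm is to be preferred when the sample is limited, and all tests are two-sided. The section names no three-group test and gives no power for either pairwise comparison.

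**The concern.** The trial is sized on one test and analysed with others. The 2-df chi-square uses all three arms at 0.05. Each key comparison has 1 df, uses two thirds of the patients, and faces a threshold of 0.025 (under Holm, 0.05 for the second step once the first succeeds). The three-group W is carried mainly by the gap between 4% and 24%, so it says little about the 4% vs 14% contrast.

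The hybrid strategy is one of three randomised arms, and the Abstract gives its unestablished benefit as part of the rationale. A reader who sees 80% power and then a non-significant hybrid vs LSRA result could take it as evidence of similar complication rates, when the planned test would often miss a difference as large as 4% vs 14%.

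**Working it through.** **Inputs.** Rates 4%, 14%, 24%; N = 175; W = 0.2353; alpha 0.05 for sizing; 15% dropout; 210 enrolled, 70 per arm (all from Sample size). Alpha 0.025 per comparison, Holm, two-sided, two comparisons against LSRA (Statistical analysis). Assumption: LSRA = 4%, hybrid = 14%, HSRA = 24%. Per-arm sizes: 175/3 ≈ 58 (the plan's evaluable number) and 70 (all enrolled).

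**1. Reproduce the plan's figure.** Mean rate = (0.04 + 0.14 + 0.24)/3 = 0.14.

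W² = (1/3)(0.10² + 0² + 0.10²) × (1/0.14 + 1/0.86) = 0.006667 × 8.3056 = 0.05537, so W = 0.2353.

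Noncentrality = N·W² = 175 × 0.05537 = 9.69. The 2-df critical value at 0.05 is 5.991, and the noncentral chi-square gives power 80.2%. At N = 174 it is just under 80%, so 175 is the minimum. Dropout: 175/0.85 = 206, and 210 covers it. The arithmetic is sound for this test.

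**2. Power of the two key comparisons.** For each pair of arms, all outcomes (x₁, x₂) were enumerated with binomial probabilities, and those where the uncorrected Pearson chi-square rejects were summed. For Holm, all three arms were enumerated jointly: a comparison is rejected if its p ≤ 0.025, or if the other has p ≤ 0.025 and its own p ≤ 0.05.

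| | 58 per arm | 70 per arm |
|---|---|---|
| HSRA vs LSRA, Bonferroni | 85.7% | 92.1% |
| HSRA vs LSRA, Holm | 86.7% | 92.7% |
| Hybrid vs LSRA, Bonferroni | 34.1% | 43.6% |
| Hybrid vs LSRA, Holm | 47.2% | 56.5% |
| At least one significant | 87.4% | 93.1% |
| Both significant, Bonferroni | 32.3% | 42.5% |
| Both significant, Holm | 46.4% | 56.0% |

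The chance of missing the hybrid difference is the complement: under Holm 1 − 0.472 = 53% to 1 − 0.565 = 44%; under Bonferroni 1 − 0.341 = 66% to 1 − 0.436 = 56%.

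**3. Sensitivity.** The pooled normal approximation at 0.025 gives 35.7% and 43.0% for hybrid vs LSRA. With no multiplicity adjustment (0.05), exact power is still only 48.5% and 57.2%. A Yates or Fisher test at 0.025 gives 23–24% and 31%.

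**4. Size needed for 80% on 14% vs 4% at 0.025** (normal approximation, pooled rate 0.09, difference 0.10):

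n = [2.2414·√(2 × 0.09 × 0.91) + 0.8416·√(0.04 × 0.96 + 0.14 × 0.86)]² / 0.10² = 154.4, i.e. 155 per arm.

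**5. Would making the omnibus test primary help?** Requiring the 2-df chi-square at 0.05 and then the pairwise test at 0.05 gives hybrid vs LSRA 46% (58 per arm) and 56% (70 per arm), essentially the Holm values.

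**The case against.** Several counter-arguments have weight.

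- **Holm, not Bonferroni.** The article names both and prefers Holm when the sample is limited. Holm also rejects whenever Bonferroni does, so the fair headline for the hybrid comparison is 47–56%, with 34–44% as the Bonferroni figure. This stands, but 56% is still far from 80%.
- **Dropout.** The primary endpoint arises during the procedure and the main analysis is intention-to-treat, so few patients should be lost from it. The relevant size is probably close to 70 per arm, although 58 is the plan's own evaluable number.
- **The rest of the trial is adequately powered.** HSRA vs LSRA exceeds 80% at both sizes, and so does the chance of at least one significant comparison. A reader might infer that the whole trial is underpowered; the figures do not support that. The shortfall is confined to one of two comparisons.
- **Non-significance as the likelier result.** A reader might also infer that a non-significant hybrid comparison is more likely than not even if the planning rates are true. That holds under Bonferroni at either size and under Holm at 58 per arm. It does not hold under Holm at 70 per arm, where power is 56%.
- **An implied omnibus test.** The general mention of a chi-square test could cover an overall three-group test before the pairwise ones. That reading is possible, but the restriction to two key comparisons points the other way. In any case, step 5 shows that it would not raise the hybrid comparison's power.
- **The 4% rate.** It is assigned to LSRA by elimination only. Reproducing W does not confirm this, because with equal arms W does not depend on which arm carries which rate.

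**Conclusion.** The point holds for one of the two key comparisons. The 80% figure is correctly calculated, but for a test that the analysis section does not name. It is met or exceeded for HSRA vs LSRA (86–92% under Bonferroni, 87–93% under Holm) and not met for HSRA + LSRA vs LSRA (47–56% under Holm, 34–44% under Bonferroni, for 58 to 70 per arm). The fault is a mismatch between the test used for sizing and the tests used for analysis; there is no error in the sample-size arithmetic.

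The figures assume that LSRA is the 4% arm, that the planning rates are true, and that the uncorrected Pearson chi-square is used; Yates or Fisher would lower the hybrid comparison further.

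**What to change.** Keep 210 patients and revise the wording:

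1. In Sample size, say which arm the 4% refers to, and that the 80% applies to the omnibus 2-df chi-square only.
2. Add the power of the tests used. With 70 per arm and Holm: about 93% for HSRA vs LSRA and about 56% for HSRA + LSRA vs LSRA. With 58 per arm: about 87% and 47%.
3. In Statistical analysis, name Holm as the single procedure for the two primary comparisons, in place of two methods and a conditional preference.
4. State that a non-significant HSRA + LSRA vs LSRA result will be reported with its confidence interval and will not be read as similar safety.
5. If the 2-df chi-square is meant to be the primary test, say so in Statistical analysis. That would align the 80% claim with a test, but the hybrid comparison's power must still be disclosed, since closed testing leaves it at about 46–56%.

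The cost is wording only, plus a less favourable stated power for one comparison. Recruitment was still under way at submission, with 132 randomised; the change should be made before analysis so that it is not a post hoc reinterpretation. Powering the hybrid comparison at 80% would need about 155 per arm (465 evaluable, or 465/0.85 ≈ 548 enrolled), which this fix does not ask for.

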### Statistical analysis

All data will be statistically analyzed using SPSS version 22.0. Quantitative data will be presented as mean ± standard deviation (± s), with intergroup comparisons made using independent sample *t*-tests. Categorical data will be presented as number (percentage) [*n* (%)], with intergroup comparisons using the χ^2^ test. Logistic regression analysis will be applied to ascertain the correlation between coronary rotational speed and perioperative complications, as well as 1-year MACCE. Considering potential data missing and loss to follow-up, we will mainly use intention-to-treat (ITT) analysis and apply per-protocol (PP) dataset for sensitivity analysis. Besides, we will preset some subgroup analyses (e.g., based on patient age groups or lesion complexity) to verify results’ stability and explore special effect participants. To account for multiple comparisons, family-wise error rate (FWER) control methods will be applied where appropriate. Specifically, Bonferroni correction (adjusting the significance threshold to *α*′ = 0.025) and the Holm-Bonferroni procedure (a stepwise approach that improves statistical power while maintaining FWER control) will be used for primary analyses. To minimize unnecessary tests, only key comparisons (HSRA vs. LSRA; HSRA + LSRA vs. LSRA) will be included. When the sample size is limited, Holm’s method will be preferred over Bonferroni to optimize the balance between statistical power and error control. A *P* value of < 0.05 will be considered statistically significant. All statistical tests will be two-sided.

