**Methods and analysis:**

This single-center, randomized controlled trial will target patients with severe coronary artery calcification scheduled for RA. An estimated 210 patients will be enrolled based on sample size calculation, randomly assigned in a 1:1:1 ratio to different rotational speed protocols using a random number table. These will include a continuous low-speed rotation (LSRA) group (140,000 rpm), a continuous high-speed rotation (HSRA) group (180,000 rpm), and a high-speed to low-speed rotation (HSRA + LSRA) group (initially 180,000 rpm, followed by 100,000 rpm). The primary endpoint is the incidence of complications during RA, including coronary artery spasm, slow/no reflow, dissection, burr entrapment, guidewire fracture, and perforation. Secondary outcomes encompass intravascular imaging (IVUS or OCT) assessments (detecting calcific ring disruption and measuring the target lesion’s minimum lumen area (MLA) and minimum lumen diameter (MLD)); in-hospital cardiac death, acute stent thrombosis, and heart failure occurrences; and the 1-year incidence of major adverse cardiovascular and cerebrovascular events (MACCE).

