It is anticipated that 210 patients who meet the inclusion and exclusion criteria will be randomly assigned in a 1:1:1 ratio to three different rotational speed groups: a continuous low-speed rotation (LSRA) group (140,000 rpm), a continuous high-speed rotation (HSRA) group (180,000 rpm), and a high-speed to low-speed rotation (HSRA + LSRA) group (initially 180,000 rpm, followed by 100,000 rpm). The study includes a 12-month follow-up period. Research protocols and documents have been distributed to relevant researchers. Recruitment began on October 1, 2023, and will continue until the estimated number of patients is reached, with the study expected to be completed within 3 years.

This study protocol has been approved by the Medical Research Ethics Committee of the First Affiliated Hospital of the University of Science and Technology of China (Anhui Provincial Hospital) under approval number 2023-KY- 076.

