This study will assess the effectiveness of coronary RA using IVUS and OCT, which provide detailed imaging of lesion structure and treatment outcomes. IVUS is a technique that uses high-frequency sound waves to visualize the inner walls of blood vessels [27]. IVUS utilizes high-frequency sound waves to visualize the inner walls of blood vessels, allowing us to accurately measure the degree of stenosis and the composition of the plaque. In this study, IVUS will assess intimal lumen diameter and plaque morphology before and after RA. This will help clarify how different rotational speeds affect the vessel wall and plaques. On the other hand, OCT uses near-infrared light to capture high-resolution images of the vessel lining [28]. OCT can provide higher resolution images than IVUS, especially in assessing intima and plaque surface characteristics. In this study, OCT will be used to assess endovascular surface features after RA treatment, including plaque tears, stenting effects, and possible vessel damage. By combining IVUS and OCT, we will be able to comprehensively evaluate the effects of RA treatment at both macroscopic and microscopic levels. This information will provide important clinical data for evaluating the safety and efficacy of different rotational speeds, thus contributing to optimize the use of RA in the treatment of coronary artery disease (CAD).

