### Planned outcomes

The primary focus of this study is to investigate the safety and efficacy of using different rotational speeds in coronary rotational atherectomy. The main endpoint is the incidence of complications during the atherectomy procedure. Secondary endpoints include assessments through intravascular imaging, in-hospital adverse cardiovascular events, and adverse cardiovascular events during the 1-year follow-up period (Table 2).

**Table 2 Tab2:** Primary and secondary endpoints

Primary endpoints	
Complications during RA	Coronary artery spasm Slow flow/no reflow Dissection Burr entrapment Guidewire fracture Perforation
Secondary endpoints	
IVUS/OCT	① Calcific ring disruption ② MLA ③ MLD
Adverse events	Cardiac death Acute stent thrombosis Heart failure
MACCE	Cardiac death Non-fatal myocardial infarction Ischemia-driven revascularization TIA

In IVUS, calcific ring disruption is defined as a loss of continuity in the calcified plaque, presenting as fissures, defects, or fractures along the plaque margins. In OCT, it is identified by cracks, defects, or fractures within the calcified region, resulting in surface irregularities or cavitations. *RA*, rotational atherectomy; *MLA*, minimum lumen area of target lesion; *MLD*, minimum lumen diameter of target lesion; *TIA*, transient ischemic attack; *MACCE*, major adverse cardiovascular and cerebrovascular events; *IVUS*, intravascular ultrasound; *OCT*, optical coherence tomography.

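### The t-test named for MLA and MLD leaves the planned pre-RA lumen measurement unused, and the multiplicity rule is not clearly extended to these endpoints

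*Protocol article*

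**What the plan says.** All references are to the protocol article.

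- **Arms (Study design).** Patients are "randomly assigned in a 1:1:1 ratio to three different rotational speed groups": low speed (LSRA), high speed (HSRA), and high followed by low speed (HSRA + LSRA).
- **Endpoints (Planned outcomes, Table 2).** The imaging secondary endpoints are calcific ring disruption, MLA and MLD. The table note defines MLA as "minimum lumen area of target lesion". The abstract allows imaging by IVUS or OCT.
- **Pre-RA measurement (Clinical procedures).** "IVUS will assess intimal lumen diameter and plaque morphology before and after RA". OCT is described only for the assessment after RA, and a pre-RA area is not named.
- **Method (Statistical analysis).** Quantitative data are summarised by mean and standard deviation, "with intergroup comparisons made using independent sample" t-tests. No ANOVA, covariate or change score is named for MLA or MLD.
- **Multiplicity (Statistical analysis).** "family-wise error rate (FWER) control methods will be applied where appropriate". Bonferroni at 0.025 and the Holm procedure "will be used for primary analyses", and "only key comparisons (HSRA vs. LSRA; HSRA + LSRA vs. LSRA) will be included". The general threshold is P < 0.05, two-sided.

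**The concern.** MLA and MLD are the trial's quantitative measures of what the burr did to the lesion. If lumen size after RA is related to lumen size before it, a comparison that ignores the starting value carries that between-patient variation in its error term. The sample size was set on the binary primary endpoint alone, so precision for MLA and MLD was never planned and any avoidable loss matters more.

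The second issue is the error rate. The correction is named for the primary analyses. For secondary quantitative endpoints the reader has only the phrase about applying control where appropriate and the general 0.05 threshold, so it is unclear which threshold a nominally positive MLA or MLD result should be judged against.

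**Working it through.** **1. The plan's own figure.** None is given for MLA or MLD. The only stated calculation is for the primary endpoint, and it reproduces. With rates of 4%, 14% and 24% in equal arms, the mean is 0.14 and W² = [(0.10² + 0 + 0.10²)/3] / (0.14 × 0.86) = 0.006667/0.1204 = 0.0554, so W = 0.2353. The 2-df chi-square at alpha 0.05 then has 80.2% power at N = 175. Dropout of 15% gives 175/0.85 = 206, which the plan rounds up to 210, or 70 per arm.

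**2. Precision.** The inputs are 70 per arm (Sample size) and a pre/post correlation r, which the documents do not give and which is varied here. With equal pre and post variances set to 1, the error variance is:

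- t-test on post-RA values: 1
- t-test on change: 2(1 − r)
- ANCOVA on the pre-RA value: 1 − r²

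| Assumed r | Post-RA | Change | ANCOVA | Patients gained against post-RA t-test, 1/(1 − r²) − 1 |
|---|---|---|---|---|
| 0.3 | 1 | 1.40 | 0.91 | 10% |
| 0.5 | 1 | 1.00 | 0.75 | 33% |
| 0.7 | 1 | 0.60 | 0.51 | 96% |

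Since 2(1 − r) − (1 − r²) = (1 − r)², which is never negative, ANCOVA is at least as precise as a change-score test as well. The degree of freedom it spends is negligible at this size.

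**3. What that means for power.** For an assumed standardised difference of 0.4 (not in the documents), 70 per arm, all with a pre-RA value, and a normal approximation:

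| Two-sided alpha | Unadjusted (post-RA) | r = 0.3 | r = 0.5 | r = 0.7 |
|---|---|---|---|---|
| 0.025 | 55% | 60% | 69% | 86% |
| 0.05 | 66% | 70% | 78% | 91% |

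**4. Incomplete baselines.** If only a fraction f of patients has a pre-RA value, and a missing indicator or mean imputation handles the rest, the pooled residual variance is about 1 − f·r². With f = 0.5 (assumed) the gain falls to 1/0.955 = 5%, 1/0.875 = 14% and 1/0.755 = 32% at r = 0.3, 0.5 and 0.7.

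**5. Family-wise error.** One million null trials were simulated at 70 per arm, with the two comparisons sharing the LSRA arm:

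| Tests, per endpoint | Family-wise error |
|---|---|
| Two key comparisons at 0.05 | 9.1% |
| Two key comparisons at 0.025 | 4.6% |
| All three pairs at 0.05 (not the plan) | 12.2% |

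Taking MLA and MLD together, two comparisons each at 0.05 give about 13% to 17%, for an assumed correlation between the two endpoints running from 0.9 down to 0.

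**The case against.** Several points on the other side stand.

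- **The three-arm comparison is not uncontrolled.** A reader might infer unrestricted pairwise testing and quote 12%. The article does not support that: the same section keeps two named comparisons and names Bonferroni and Holm. Only the reach of that rule beyond the primary analyses is unclear.
- **Pairwise t-tests are not invalid here.** With two planned contrasts no omnibus test is needed. Using two arms' variance in place of three gives 138 degrees of freedom against 207, a critical t of about 1.98 against 1.97.
- **The article does not say that raw post-RA values are tested.** A reader might assume so, but it names a test and not the quantity. It discusses earlier work in terms of lumen gain, so a test on change is also possible. The precision argument holds on either reading.
- **The baseline is not documented for everyone.** It is stated for diameter by IVUS, not for area or OCT. The eligibility criteria admit lesions that a balloon cannot pass, so some pre-RA images may not exist.
- **The correlation is assumed.** At r = 0.3 the gain is modest.

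It can also be said that a journal article leaves covariate adjustment to the full plan, and that secondary endpoints often go without strict error control. The first does not dispose of the point, because the article does not stay silent: it fixes a method for all quantitative data. The second is fair, and is why an exploratory label is an acceptable answer.

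**Conclusion.** The point holds as a matter of efficiency and clarity. The stated method for MLA and MLD is a two-sample t-test, and no stated analysis adjusts for a pre-RA measurement that the trial plans to take, at least for IVUS diameter. Randomisation protects against bias, so the cost is precision: the equivalent of about 10% to 96% more patients for r between 0.3 and 0.7 if every patient has a baseline, and less if some do not. Both r and the share of patients with a usable pre-RA image are assumptions.

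On multiplicity, the conclusion is limited to scope. If the named correction does not reach MLA and MLD, the two key tests carry about 9% family-wise error per endpoint; if it does, about 4.6%. The primary endpoint and its sample size are unaffected.

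**What to change.** Analyse post-RA MLA and MLD by ANCOVA, with arm as a three-level factor and the pre-RA value and imaging modality (IVUS or OCT) as covariates. Where no pre-RA image exists, use a missing-baseline indicator or mean imputation of the baseline, so that no randomised patient is dropped for lacking a covariate. Where only a pre-RA diameter is available, it can also serve as the covariate for MLA.

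Report the two key contrasts (HSRA vs LSRA; HSRA + LSRA vs LSRA) with 95% confidence intervals. State either that the Holm rule applies to them or that they are exploratory.

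The cost is a few sentences in the analysis plan, a small handling rule for missing pre-RA images, and slightly more analysis work with a standard general linear model in SPSS. It needs no extra patients or measurements. The change should be dated before allocation is released to the analysts.

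### The plan does not fix one decision rule for its two key comparisons; naming Holm without conditions would gain power at no cost in type I error

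*Protocol article*

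**What the plan says.** All the relevant text is in the protocol article, section Statistical analysis.

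- Scope of the control: "family-wise error rate (FWER) control methods will be applied where appropriate".
- Family: "only key comparisons (HSRA vs. LSRA; HSRA + LSRA vs. LSRA) will be included". That is two comparisons sharing the LSRA arm. Sidedness: "All statistical tests will be two-sided".
- First procedure: "Bonferroni correction (adjusting the significance threshold to" 0.025.
- Second procedure, joined to the first by 'and': "the Holm-Bonferroni procedure (a stepwise approach that improves statistical power while maintaining FWER control) will be used for primary analyses".
- Choice between them: "When the sample size is limited", Holm's "method will be preferred over Bonferroni to optimize the balance between statistical power and error control". No number, time point or decision-maker is attached to the condition.
- Closing line: a P "value of < 0.05 will be considered statistically significant". It does not mention adjusted P values or the primary family.

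**The concern.** Bonferroni and Holm are alternatives for the same two tests. When their verdicts differ, only one can stand, and the plan's only tie-breaker is an undefined sample-size condition. The planned total is fixed at 210, and a reader cannot tell whether 210, or some shortfall from it, counts as limited. The condition also has no statistical basis. Holm controls the family-wise error at every sample size and rejects everything that Bonferroni rejects, and the section itself credits it with more power under the same control.

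The closing 0.05 line adds a second uncertainty. Read as applying to adjusted P values, or to tests outside the family, it is harmless. Read as applying to the raw P values of the two key comparisons, it bypasses the correction. At stake is mainly the verdict on HSRA + LSRA vs LSRA, the weaker of the two planned contrasts on the protocol's own rates.

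**Working it through.** **Inputs.** Sample size section: rates 4%, 14% (HSRA + LSRA) and 24% (higher speeds); W = 0.2353; N = 175 for 80% power in a 2-df chi-square test at 0.05; 15% dropout; 210 in total, 70 per group. Statistical analysis section: two comparisons against LSRA, two-sided, Bonferroni threshold 0.025. The Sample size section names no arm for the 4%. I assign it to LSRA because the other two rates are taken.

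**1. The plan's own figures.**
- Mean rate = (0.04 + 0.14 + 0.24)/3 = 0.14.
- W² = [(0.10² + 0² + 0.10²)/3] / (0.14 × 0.86) = 0.006667/0.1204 = 0.05537, so W = 0.2353, as stated.
- Noncentral chi-square power with 2 df at N = 175 is 80.2%; at N = 174 it is just under 80%. The 175 reproduces.
- 175/0.85 = 206, close to the stated 210.
- 0.05/2 = 0.025, as stated for Bonferroni.

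The 80% belongs to the three-group test, not to either pairwise comparison.

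**2. The candidate rules.** Let p(1) ≤ p(2) be the two P values.
- Bonferroni: reject each comparison with p < 0.025.
- Holm: reject p(1) if p(1) < 0.025; if so, reject p(2) if p(2) < 0.05.
- Raw 0.05: reject each comparison with p < 0.05.

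Bonferroni and Holm treat p(1) identically, so they always agree on whether anything is significant. They differ only when p(1) < 0.025 and p(2) lies between 0.025 and 0.05.

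**3. Two worked results, 70 per arm** (uncorrected chi-square, pooled variance).
- LSRA 3 events, HSRA + LSRA 10, HSRA 17. For hybrid vs LSRA the pooled rate is 13/140 = 0.0929, SE = √(0.0929 × 0.9071 × 2/70) = 0.0491, z = 0.100/0.0491 = 2.04, P = 0.0415. For HSRA vs LSRA, P = 0.0007. The hybrid comparison fails under Bonferroni and passes under Holm.
- LSRA 3, HSRA + LSRA 10, HSRA 9. P = 0.0415 and 0.0701. Nothing is significant under Bonferroni or Holm; the hybrid comparison passes only under raw 0.05.

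**4. How often this matters.** 400,000 simulated trials per setting, rates LSRA 4%, HSRA + LSRA 14%, HSRA 24%, at 70 per arm (full enrolment) and 58 per arm (175/3).

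| | 70 per arm | 58 per arm |
|---|---|---|
| Power, hybrid vs LSRA: Bonferroni / Holm / raw 0.05 | 43.6 / 56.4 / 57.1% | 34.0 / 47.2 / 48.5% |
| Power, HSRA vs LSRA: Bonferroni / Holm / raw 0.05 | 92.1 / 92.6 / 95.6% | 85.8 / 86.7 / 91.5% |
| Both significant: Bonferroni / Holm | 42.6 / 56.0% | 32.3 / 46.5% |
| Trials where Bonferroni and Holm differ | 13.4% | 14.1% |
| Trials where Holm and raw 0.05 differ | 3.3% | 5.3% |

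**5. Family-wise error when neither comparison has a true difference.** Normal theory, correlation 0.5 from the shared LSRA arm: Bonferroni or Holm 4.6%, raw 0.05 on both 9.1%. If the tests were independent, raw 0.05 would give 1 − 0.95² = 9.75%; the upper bound is 10%. Binomial simulation at a common 14% rate: 4.6% and 8.8% at 70 per arm, 4.7% and 9.1% at 58 per arm.

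**The case against.** A reader might infer three incompatible rules and an analyst free to pick among them once the P values are known. The documents do not support that.

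- **Bonferroni and Holm are nested.** Even a choice made after seeing the results could reject no more than Holm rejects, so the family-wise error stays at or below 5%. The 13 to 14% disagreement is a power difference on a second comparison, not a count of false positives.
- **The 0.05 line is general.** It follows explicit instructions for the primary family and fits as the overall level, as the threshold for adjusted P values, or as the rule for other tests. To say that it removes the control altogether, one must let a generic sentence override the specific ones. The 9% is conditional on that reading.
- **The stated trigger is sample size, not results.** The number enrolled is known before analysis, and the Randomization section says that allocation data are held by an independent team with blinding until analysis is complete. Nothing says that the choice is made after the fact.
- **This is a condensed article.** An analysis plan that is not shown may define the condition and the testing steps.

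The first three points stand and limit the finding. The fourth stands only in part: the article does not merely leave the rule open, it states a conditional one, and the condition serves no purpose at any sample size. The missing link between the 0.05 line and adjusted or raw P values also remains.

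**Conclusion.** The point holds as a matter of unfixed wording with an avoidable loss of power. Where p(1) < 0.025 and p(2) lies between 0.025 and 0.05, the plan does not determine the verdict on the second comparison. On the protocol's rates this happens in 13.4% of trials at 70 per arm and 14.1% at 58. For HSRA + LSRA vs LSRA at 70 per arm, Holm gives 56.4% power against 43.6% for Bonferroni, a gain of 12.8 points with the same bound on type I error. The choice between the two is not a threat to error control. The rise to about 9% arises only if 0.05 is applied to raw P values of both comparisons and neither has a true difference. The power and disagreement figures rest on the 4% rate belonging to LSRA and on uncorrected chi-square tests. Severity: minor to moderate.

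**What to change.** In the Statistical analysis section:

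1. Name one procedure for the two key comparisons: Holm at family-wise 0.05, two-sided, regardless of sample size.
2. Delete the Bonferroni alternative and the sentence that makes Holm depend on a limited sample size.
3. State that P < 0.05 refers to Holm-adjusted P values within the primary family, and to unadjusted P values only for analyses outside it. For two comparisons the adjusted values are min(1, 2 × p(1)), and the larger of that and p(2).

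The cost is a few lines of protocol or analysis-plan wording, to be settled before unblinding. It needs no further patients and loses no power relative to Bonferroni.
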